#### **Efficacy Evaluation:**

According to RECIST 1.1 criteria for solid tumor efficacy, evaluating the efficacy of aumolertinib combined with apatinib versus aumolertinib alone in first-line treatment of advanced NSCLC subjects with *EGFR* sensitive mutations.

Efficacy endpoint:

1. Primary endpoint: 18-month PFS rate.
2. Secondary endpoints: PFS, confirmed ORR, DoR, safety, and OS.
3. Exploratory endpoints: PFS benefits in patients with CNS metastasis, *EGFR* exon 19 deletion, *EGFR* L858R mutation, and other mutational events.

#### **Safety Evaluation:**

Observe and record any adverse events experienced by subjects during the clinical trial period, including clinical symptoms, abnormal vital signs, and abnormal laboratory tests; record severity, time of onset, duration, treatment method, and prognosis; and determine its relatedness to the study drug. Safety endpoints: Occurrence of adverse events; occurrence of serious adverse events; proportion of dose modification, patients withdrawn or due to adverse events.

#### **Calculation of Sample Size:**

Given assumptions of 18-month PFS rate of 75% for aumolertinib plus apatinib and 50% for aumolertinib alone, a drop-out rate of 10%, at the significance level of 0.05, to achieve the power of 0.8, a total number of 98 subjects are needed (49 per arm).

### **3. Table of Abbreviations**

|                    |                                                                |
|--------------------|----------------------------------------------------------------|
| AE                 | Adverse Event                                                  |
| ALT                | Alanine aminotransferase                                       |
| APTT               | Activated partial thromboplastin time                          |
| AST                | Aspartate aminotransferase                                     |
| C1D1               | Cycle 1 Day 1                                                  |
| CI                 | Confidence interval                                            |
| CNS                | central nervous system                                         |
| CR                 | Complete response                                              |
| CT                 | Computed tomography                                            |
| CTCAE              | Common Terminology Criteria for Adverse Events                 |
| CYP                | Cytochrome P450                                                |
| DCR                | Disease control rate                                           |
| DLT                | Dose limiting toxicity                                         |
| DNA                | Deoxyribonucleic acid                                          |
| DoR                | Duration of response                                           |
| ECG                | Electrocardiogram                                              |
| ECOG               | Eastern Cooperative Oncology Group                             |
| EGFR               | Epidermal growth factor receptor                               |
| EGFR m+ | Epidermal growth factor receptor sensitizing mutation positive |
| FAS                | Full analysis set                                              |
| FSH                | Follicle-stimulating hormone                                   |
| HIV                | Human immunodeficiency virus                                   |
| HR                 | Hazard ratio                                                   |
| IDMC               | Independent Data Monitoring Committee                          |
| INR                | International normalized ratio                                 |
| LH                 | Luteinizing hormone                                            |
| LVEF               | Left ventricular ejection fraction                             |

|                    |                                                                                      |
|--------------------|--------------------------------------------------------------------------------------|
| mPFS               | Median progression-free survival                                                     |
| MRI                | Magnetic resonance imaging                                                           |
| MTD                | Maximum tolerated dose                                                               |
| NE                 | Not evaluable                                                                        |
| NSCLC              | Non-small cell lung cancer                                                           |
| ORR                | Objective response rate                                                              |
| OR                 | Odds ratio                                                                           |
| OS                 | Overall survival                                                                     |
| PFS                | Progression-free survival                                                            |
| PD                 | Progressive disease                                                                  |
| PET-CT             | Positron emission tomography and X-ray computed tomography system                    |
| PK                 | Pharmacokinetics                                                                     |
| PR                 | Partial response                                                                     |
| QD                 | Once daily                                                                           |
| QT                 | ECG interval measured from the beginning of the QRS complex to the end of the T wave |
| QTc                | Corrected QT interval                                                                |
| QTcF               | Fridericia-corrected QTc                                                             |
| RECIST 1.1         | Response Evaluation Criteria in Solid Tumors (version 1.1)                           |
| SAE                | Serious adverse event                                                                |
| SD                 | Stable disease                                                                       |
| T790M              | Mutation of amino acid at position 790 in EGFR from threonine to methionine   |
| T790M + | T790M mutation positive                                                              |
| TL                 | Target lesion                                                                        |
| TKI                | Tyrosine kinase inhibitor                                                            |

|     |                       |
|-----|-----------------------|
| ULN | Upper limit of normal |
|-----|-----------------------|

## 4. Research Background and Scientific Basis

### 4.1 Background

Lung cancer is one of the most common malignancies in the world. In 2018, cancer data from China indicated that lung cancer had the highest incidence and mortality rates, accounting for more than 20%. Non-small cell lung cancer (NSCLC) accounts for 80%-85% of all lung cancers, approximately 70% of lung cancer patients are already at an advanced stage, either locally or with distant metastasis, by the time of initial diagnosis, making surgical resection unfeasible. Additionally, patients who initially undergo successful surgical resection later develop distant metastases by the time of relapse. The median survival of patients with advanced NSCLC who cannot be surgically resected is often less than one year.

Epidermal growth factor receptor (*EGFR*) sensitive mutations (*EGFRm+*) are the most common driver gene mutations in NSCLC, accounting for 10%-17% of Western populations and 30%-50% of Asian populations. Tyrosine kinase inhibitors (TKI) targeting *EGFR*-sensitive mutations have become the first-line standard treatment for locally advanced or metastatic NSCLC with *EGFRm+*, with progression-free survival (PFS) of 8-18.9 months. But patients who initially respond to EGFR-TKIs will inevitably develop disease progression due to secondary resistance. Therefore, it is urgent to delay or overcome EGFR-TKIs resistance, improve patients' PFS and overall survival (OS), and explore new treatment options.

Vascular endothelial growth factor receptor (VEGFR) is a signaling pathway parallel to *EGFR* but intersecting downstream. VEGFR tyrosine kinase inhibitors inhibit the VEGFR signaling pathway, control tumor angiogenesis, and may play a role in EGFR-TKI resistance. The combination of anti-angiogenic agents and EGFR-TKI, inhibiting both VEGFR and EGFR pathways, improves the response to

targeted therapy and delays the onset of acquired resistance in NSCLC patients.

Currently, the combination therapy of anti-angiogenic drugs and EGFR-TKI (also known as "A+T" combination therapy) has been shown to be effective in NSCLC. Domestic and foreign guidelines such as ESMO and CSCO have recommended "A+T" as the first-line treatment for *EGFR* driver gene positive in advanced NSCLC patients .

In February 2011, the JO25567 study (randomized, controlled, Phase II study) conducted in Japan, compared erlotinib plus bevacizumab versus erlotinib alone in the first-line treatment of 154 Japanese patients with advanced *EGFR*-sensitive mutated non-squamous NSCLC. The results showed that "A+T" significantly prolonged patients' PFS (16.0 months vs 9.7 months,  $P=0.0015$ ) . The subsequent NEJ026 study (randomized, controlled, Phase III study) enrolled 228 patients who received bevacizumab plus erlotinib or erlotinib alone. The results showed that PFS was 3.6 months longer in the combination group than in the monotherapy group (16.9 months vs 13.3 months,  $P=0.016$ ). The RELAY study (global, double-blind, Phase III clinical trial) compared the efficacy and safety of erlotinib plus ramucirumab with erlotinib alone in patients with stage IV or post-operatively relapsed *EGFR* in 449 global participants. Results showed that the "A+T" group significantly extended patients' median progression-free survival (mPFS) by 7 months (19.4vs 12.4,  $P<0.0001$ ) .

However, in the above combination study protocol, both bevacizumab and ramucirumab required intravenous administration, which undoubtedly increased the number of repeated admissions and visits of patients, and had a certain impact on the quality of life. The ACTIVE study combining apatinib with gefitinib is currently underway. Dual-target oral "A+T" regimen provides patients with advanced NSCLC with more options and better quality of life. However, more high-quality evidence-based medical evidence is needed to support this approach.

Aumolertinib (HS10296) is a class 1 new drug independently developed by

Jiangsu Hansoh Pharmaceutical Group Co., LTD. The third generation of small molecule EGFR-TKI, which can irreversibly and highly selectively inhibit *EGFR* sensitive mutations (such as exon 19 deletion and L858R mutation) and Mutation of amino acid at position 790 in *EGFR* from threonine to methionine (T790M) resistant mutations. At the same time, the activity against wild-type *EGFR* is minimal, resulting in a low incidence of adverse reactions.

Apatinib (YN968D1) is a new targeted drug developed and produced in China, and the world's first effective and safe small-molecule anti-angiogenesis targeted drug for gastric cancer. A previous multicenter Phase II study of 105 patients with advanced NSCLC confirmed that Apatinib is efficacy and tolerable in pretreated patients with advanced NSCLC .

Therefore, this study aims to evaluate the efficacy and safety of aumolertinib plus apatinib versus aumolertinib alone in first-line treatment of advanced NSCLC with epidermal growth factor receptor-sensitive mutation (*EGFR*m+).

## **4.2 Scientific Evidence**

Aumolertinib has been granted new drug clinical trial approvals by both the U.S. Food and Drug Administration and the National Medical Products Administration in mainland China and is currently undergoing international multicenter Phase I/II trials. The phase I study is an open, multicenter study in patients with locally advanced or metastatic NSCLC whose disease has progressed following prior EGFR-TKI treatment, including dose escalation and dose extension.

The single-dose Pharmacokinetics (PK) data of aumolertinib in advanced NSCLC patients who had progressed after previous EGFR-TKI treatment showed that aumolertinib was absorbed quickly after a single fasting oral administration, the blood concentration peaked at 4.0 hours, and the mean drug elimination half-life ranged from 30.7 to 37.5 hours. In the dose range of 55mg to 220 mg, the PK parameters Cmax and AUC of aumolertinib were linearly correlated with the dose. The exposure of active metabolite HAS-719 (major circulating metabolite of HS10296) was about 1/3

of that of the original drug, and the PK parameters showed a linear relationship. The peak time of HAS-719 was about 6 hours later than that of the original drug, and the half-life of the drug elimination was 50-70 hours. The PK test data showed that the plasma concentration of aumolertinib reached a stable state after 7 consecutive days of once-daily administration (QD). Compared with a single dose, there was almost no accumulation in steady state. In the dose range of 55mg to 220mg, when continuous administration reached homeostasis, aumolertinib exposure had a linear relationship with steady-state blood concentration and area under the curve.

A total of 26 patients were included in the phase I dose escalation trial of aumolertinib. No dose limiting toxicity (DLT) occurred in the low-dose group (55/110mg), only 1 of 6 patients in the 220mg dose group had DLT (grade 3 anemia), and only 1 of 6 patients in the 260mg dose group had DLT, grade 3 creatinine elevation; The maximum tolerated dose (MTD) was not reached in the dose escalation phase. Overall objective response rate (ORR) and disease control rate (DCR) were 52.4% and 85.7% for patients eligible for interim evaluation (n=21). In the 55mg (6 cases) and 110mg (6 cases) dose groups, the ORR was 66.7% and DCR was 100.0%. In the 220mg dose group (6 cases), ORR was 50.0%, DCR was 83.3%, and in the 260mg dose group, only 3 cases completed treatment response assessment, DCR was 33.3%.

The Phase I extension study of aumolertinib has completed enrollment in a T790M mutation-positive population, with a total of 91 participants enrolled in the 55mg (30 cases), 110mg (30 cases), and 220mg (31 cases) dose groups. In terms of safety, the common adverse events (AEs) was rash, fatigue, blurred vision, decreased white blood cells, gastrointestinal symptoms (such as constipation, diarrhea, nausea), and elevated levels of creatine kinase and alanine aminotransferase. However, symptoms were mild or asymptomatic, and most AEs resolved on their own. No drug-related serious AEs (SAEs) occurred in the 55mg and 110mg dose groups. In the 220mg dose group, the incidence and severity of AE increased significantly. In terms

of treatment response, among patients eligible for interim evaluation (n=76), overall ORR was 50.0% and DCR was 92.1%. In the 55mg dose group (30 cases), ORR was 53.3% and DCR was 83.3%. The ORR and DCR of 110mg (30 cases) were 46.7% and 96.7% respectively. In the 220mg dose group (16 cases), ORR was 50.0% and DCR was 100.0%.

The data of 55mg and 110mg in the dose escalation phase and the extension phase were combined for analysis: In the phase I clinical trial of the second-line treatment of advanced NSCLC, 36 patients with T790M mutation-positive were enrolled in the 55mg and 110mg dose groups respectively, and the last patient was followed up for 3 months after enrollment. All patients had been evaluated for efficacy at least twice. At present, there are no unintended safety concerns in either dose group. The overall ORR for T790M mutation was 52.1%, 55.6% in the 55mg dose group and 50.0% in the 110mg dose group. The overall DCR was 92.6%, including 86.1% in the 55mg dose group and 97.2% in the 110mg dose group.

The results of the Phase II single-arm clinical study of aumolertinib were announced at the 2019 World Congress on Lung Cancer (WCLC). The study enrolled 244 patients with locally advanced or metastatic NSCLC with *EGFR* T790M mutation, as well as asymptomatic BMS, and showed an ORR of 68.4%, DCR was 93.4%; The 12-month progression-free survival rate was 53%. Aumolertinib was well tolerated, and the most common adverse events were elevated of creatine phosphokinase, rash, pruritus, elevated of AST/ ALT, anemia, and decreased white blood cell count. Grade 3 or higher drug-related adverse events occurred in 20.9% patients, and no interstitial pneumonia was reported.

In addition, the randomized, double-blind, controlled phase III clinical study of aumolertinib versus gefitinib in first-line treatment of advanced NSCLC with *EGFR* mutations (NCT03849768) is ongoing, with enrollment of 350 participants completed in October 2019, and the primary endpoint reached statistically significant positive results. Specific data will also be presented at international academic conferences in

due course.

Aumolertinib ® (Aumolertinib mesylate tablet) is a class 1 innovative drug independently developed by Jiangsu Hansoh Pharmaceutical Group Co., LTD., and has been approved by the National Medical Products Administration (NMPA) on March 18 (approval number: H20200004) for the treatment of "adult subjects with locally advanced or metastatic NSCLC who have experienced disease progression during or after prior treatment with EGFR-TKI and have been tested positive for *EGFR* T790M mutation."

Based on the above research and the clinical data of aumolertinib, we designed this study to evaluate the efficacy and safety of aumolertinib plus apatinib versus aumolertinib alone in first-line treatment of advanced NSCLC with *EGFR*m+.

## 5. Study Endpoints

The endpoints of this study will be analyzed based on the tumor response assessment by investigator per Response Evaluation Criteria in Solid Tumors (version 1.1) (RECIST 1.1).

Primary endpoint is 18-month PFS rate.

Secondary endpoints consist of PFS, confirmed objective response rate (ORR, the proportion of patients with confirmed complete response or partial response), duration of response (DoR, time from the first documented response to the first time of disease progression or death), safety, and OS.

Exploratory endpoints consist of PFS benefits in patients with central nervous system (CNS) metastasis, *EGFR* ex19del, *EGFR* L858R mutation, and other mutational events.

## 6. Sample Size

This is a multicenter, randomized, open-label study with a superiority design. The primary endpoint is 18-month PFS rate. Based on the assumptions of 18-month PFS rate of 75% for aumolertinib plus apatinib and 50% for aumolertinib alone, a drop-out rate of 10%, at the significance level of 0.05, to achieve the power of 0.8, a

total number of 98 subjects are needed (49 per arm).

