## **10. Statistical Analytical Methods**

To assess the between-group differences, we will use (i) the Chi-square test for categorical variables, (ii) the Mann-Whitney test for continuous variables, (iii) the Kaplan-Meier method and the Log-rank test for time-to-event variables, and (iv) the “naïve” test based on the comparison of Kaplan-Meier estimators for the 18-month PFS rate (“Fixpoint.test” function of the R package: ComparisonSurv). Hazard ratios (HRs) and corresponding 95% confidence intervals (CIs) will be estimated using the Cox proportional hazards model. The 95% CIs for ORR will be generated through the Clopper-Pearson method. Univariable and multivariable analyses of PFS and ORR will be performed with the Cox proportional hazards model and the logistic regression model, respectively. The interaction effect between treatment and each key variable will be calculated using a Cox proportional hazards model (for PFS) or a logistic regression model (for ORR) that contains the treatment group, key variable, and treatment-by-variable interaction term. All statistical analyses mentioned above will

be performed using IBM SPSS Statistics 22 or R 4.1.3.

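### The 98 patients match 80% power only at a one-sided 0.05 level, which the protocol never states; at two-sided 0.05 the power is about 73%

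*Protocol*

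**What the plan says.** Section 6 of the protocol describes the design: "This is a multicenter, randomized, open-label study with a superiority design". It assumes an "18-month PFS rate of 75% for aumolertinib plus apatinib and 50% for aumolertinib alone", adds 10% for drop-out, and sets the error rates as "at the significance level of 0.05, to achieve the power of 0.8". From these it concludes: "a total number of 98 subjects are needed (49 per arm"). The synopsis, under Calculation of Sample Size, repeats the same inputs and the same total.

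Neither place says whether the level is one- or two-sided. Section 10.1.1 names the primary test, the naive comparison of the two Kaplan-Meier estimates at 18 months, but gives no side, no success threshold and no interval for the difference. The only interval level in the protocol is 95%. Section 10 says of the hazard ratios that "corresponding 95% confidence intervals (CIs) will be estimated using the Cox proportional hazards model", and it uses 95% intervals for the response rate as well.

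**The concern.** A level of 0.05 with no qualifier, in a two-arm superiority trial that reports 95% intervals, is normally applied two-sided. On that reading the stated inputs do not lead to 98 patients, and the stated power is not delivered. On the one-sided reading the inputs do lead to 98, but the reader is not told that the threshold is the equivalent of two-sided 0.10.

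The gap matters for the decision. With 44 evaluable patients per arm and the planning variance, the standard error of the difference is √(0.4375/44) = 0.0997. Significance then needs an observed difference of about 1.645 × 0.0997 = 16 percentage points one-sided, or 1.960 × 0.0997 = 20 points two-sided. A result between these succeeds on one reading and fails on the other. The trial is open-label with investigator-assessed progression, so the rule should be fixed before the arms are compared.

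**Working it through.** **Inputs (Section 6 and synopsis).** p1 = 0.75, p2 = 0.50, difference 0.25, level 0.05, power 0.80, drop-out 10%, 1:1 allocation, 49 per arm. After 10% loss, 49 × 0.9 = 44.1, so 44 evaluable per arm.

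**Reproducing 98.** The unpooled two-proportion formula is

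n per arm = (z_α + z_β)² × [p1(1−p1) + p2(1−p2)] / (p1−p2)²

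The bracket is 0.1875 + 0.25 = 0.4375. Divided by 0.25² = 0.0625, it gives 7.

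- One-sided 0.05: (1.645 + 0.842)² = 6.183, and 6.183 × 7 = 43.28, rounded up to 44. Then 44/0.9 = 48.9, rounded up to 49 per arm, **98 in total: an exact match**.
- Two-sided 0.05: (1.960 + 0.842)² = 7.849, and 7.849 × 7 = 54.94, rounded up to 55. Then 55/0.9 = 61.1, rounded up to 62 per arm, 124 in total.

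**Other formulas.** Totals after 10% drop-out:

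| Formula | One-sided 0.05 | Two-sided 0.05 |
|---|---|---|
| Unpooled proportions | 98 | 124 |
| Pooled proportions | 104 | 130 |
| Arcsine | 104 | 130 |
| Log-log transformed survival | 110 | 140 |
| Log transformed survival | 114 | 144 |
| Log-rank events, Schoenfeld | about 95 | about 122 |
| Log-rank events, Freedman | about 110 | about 137 |

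No two-sided version comes near 98. Even with no drop-out, the smallest two-sided total is about 110.

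**Power with the stated 98 patients.** For the unpooled formula, power = Φ(0.25/SE − z_α):

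- 44 per arm, two-sided: 0.25/0.0997 = 2.507; 2.507 − 1.960 = 0.547; power 70.8%.
- 44 per arm, one-sided: 2.507 − 1.645 = 0.862; power 80.6%.
- 49 per arm (no loss), two-sided: SE = √(0.4375/49) = 0.0945; 2.646 − 1.960 = 0.686; power 75.4%.

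The pooled formula gives 68.4% (44 per arm) and 73.1% (49 per arm) two-sided, and 78.9% one-sided at 44 per arm. Exact binomial enumeration of the z-tests, two-sided, gives 70-72% at 44 per arm and 73-75% at 49.

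**The planned test.** A Kaplan-Meier comparison uses the follow-up of censored patients, so dropping 10% outright is slightly pessimistic. The simulation assumes 49 per arm, exponential PFS, 10% of patients given a censoring time spread uniformly over 18 months, and an untransformed difference with Greenwood variances:

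- two-sided 0.05: power 72.6-73.0%
- one-sided 0.05: power 81.7-82.2%
- two-sided with no loss: power 74.9%

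**The case against.** Four points can be made for the protocol.

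- **One-sided 0.05 may simply be what was meant.** It is the only basis that returns 98 exactly, which is internal evidence that it was used, and on it the level, power and sample size agree. This stands. A reader might infer that 98 is a calculation error, and the documents do not support that: what is missing is the label. A reader might also infer that the type II error is 27% or more. That follows only if the test is two-sided, which the protocol does not say.
- **The 95% intervals do not fix the side of the primary test.** This also stands. They belong to hazard ratios and response rates, and Section 10.1.1 gives no interval for the 18-month difference. They suggest how a reader will take 0.05; they do not settle it.
- **A statistical analysis plan may state the side.** It may, and that plan is not at hand, so nothing here shows that the choice is still open. But Section 6 reports its own calculation, and its stated inputs do not determine its stated result without the side.
- **One-sided 0.05 can be acceptable in phase II.** That is not disputed. The objection is to relying on it without saying so.

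**Conclusion.** The concern holds as an unlabelled significance level, not as faulty arithmetic. The 98 patients are reproduced exactly only with one-sided 0.05 and unpooled variance.

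- **If 0.05 is one-sided,** power is about 79-82% with 10% loss and the stated 0.8 stands. The level then equals two-sided 0.10 and should be declared as such.
- **If 0.05 is two-sided,** power is about 73% for the planned 18-month comparison with 10% loss (68-75% across formulas and 44 to 49 per arm), and the stated 0.8 is not met.

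The 73% rests on the protocol's 75% and 50%, and on the assumed exponential PFS and evenly spread drop-out. The shortfall under a two-sided test does not depend on those last two assumptions: every formula and the exact calculation also fall below 80%.

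**What to change.** Make the same change in the synopsis, Section 6 and Section 10.1.1, before any comparison of outcomes by arm. Choose one:

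1. **One-sided.** State that 98 rests on one-sided alpha 0.05, that success means a one-sided p-value below 0.05 in favour of the combination, and that a two-sided 90% CI for the 18-month PFS difference accompanies it. Add a line explaining why this interval differs from the 95% intervals used elsewhere.
2. **Two-sided.** State two-sided 0.05, keep 98 patients, and restate the power as about 73% (range 68-75%).

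The first keeps the stated power and makes the more lenient level visible. The second keeps the conventional level and lowers the stated power. Either costs a sentence or two in three places and no extra patients.
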